**LIST OF ABBREVIATIONS AND RELEVANT DEFINITIONS**

|                |                                                                                                                    |
|----------------|--------------------------------------------------------------------------------------------------------------------|
| ACL     | Anterior Cruciate Ligament                                                                                  |
| ADL     | Activities of Daily Living                                                                                  |
| AE      | Adverse Event                                                                                               |
| APM     | Arthroscopic Partial Meniscectomy                                                                           |
| AR      | Adverse Reaction                                                                                            |
| ASA     | American Society of Anesthesiologists                                                                       |
| BMI     | Body Mass Index                                                                                             |
| CCMO    | Central Committee on Research Involving Human Subjects; in Dutch: Centrale Commissie Mensgebonden Onderzoek |
| CV      | Curriculum Vitae                                                                                            |
| DSMB    | Data Safety Monitoring Board                                                                                |
| EudraCT | European drug regulatory affairs Clinical Trials                                                            |
| GCP     | Good Clinical Practice                                                                                      |
| HLQ     | Health and Labour Questionnaire                                                                             |
| IC      | Informed Consent                                                                                            |
| ICRS    | International Cartilage Repair Society                                                                      |
| IKCD    | International Knee Documentation Committee                                                                  |
| ISAKOS  | International Society of Arthroscopy, Knee Surgery and Orthopedic Sports Medicine                           |
| KOOS    | Knee injury and Osteoarthritis Outcome Score                                                                |
| MREC    | Medical research ethics committee (MREC); in Dutch: Medisch Ethische Toetsing Commissie (METC)              |
| MRI     | Magnetic Resonance Imaging                                                                                  |
| OA      | OsteoArthritis                                                                                              |
| PSC     | Patient Specific Complaints (in Dutch: Patiënt Specifieke Klachten)                                         |
| PE      | Physical Examination                                                                                        |
| QOL     | Knee-related Quality Of Life                                                                                |
| (S)AE   | (Serious) Adverse Event                                                                                     |
| SPC     | Summary of Product Characteristics (in Dutch: officiële productinformatie IB1-tekst)                        |
| SUSAR   | Suspected Unexpected Serious Adverse Reaction                                                               |
| Wbp     | Personal Data Protection Act (in Dutch: Wet Bescherming Persoonsgegevens)                                   |
| TiC-P   | Trimbos/iMTA questionnaire for Costs associated with Psychiatric Illness (TiC-P)                            |
| VAS     | Visual Analogue Scale                                                                                       |
| WMO     | Medical Research Involving Human Subjects Act (in Dutch: Wet Medisch-wetenschappelijk Onderzoek met Mensen) |

## 2. SUMMARY

**Rationale:** Current standard treatment of symptomatic non-obstructive meniscal tears in older patients is surgery. Annual costs are 33 million Euros in this patient group (N=15.000) in the Netherlands. Nevertheless, evidence is lacking that supports its superiority over conservative treatment. When conservative treatment is non-inferior to surgery, this strategy alone could save over 12 million Euros on an annual basis.

We therefore risk large healthcare inefficiency, since these patients are treated surgically. The financial benefits of conservative treatment might even be enhanced by an anticipated decrease in the progression to knee osteoarthritis, since fewer knee arthroplasties would be necessary. This could even further decrease the annual costs spent on knee surgeries.

**Objective:** This multicenter randomized controlled trial is designed to compare surgical to conservative treatment of non-obstructive meniscal injuries in older patients.

**Hypothesis:** We assume equal improvement of physical function in both groups and reduced costs with conservative treatment.

**Study design:** Non-inferiority multicenter randomized controlled trial with an economic evaluation alongside. The study will be conducted by the Orthopaedic Research Consortium Mid-West Netherlands and performed in 9 clinics, including 1 academic medical center.

**Study population:** We will include 320 patients between 45 and 70 years with MRI-confirmed symptomatic, non-obstructive meniscal tears. Two groups 160 patients, are needed to prove non-inferiority of conservative therapy. Block randomization will be done web-based.

**Measurements:** Patients will be asked to complete questionnaires at baseline and 3, 6, 9, 12, 18 and 24 months. At 3 months they will visit the outpatient department for physical examination. At 24 months an X-ray will be obtained. We also plan a follow-up at 60 months.

**Primary outcome:** Physical function, measured by International Knee Documentation Committee 'Subjective Knee Form'.

**Secondary outcome:** general health (RAND-36), quality of life (EQ-5D5L), level of activity (Tegner Activity Scale), knee pain on Visual Analogue Scale (VAS), productivity losses and the use of healthcare services (TiC-P), patient specific complaints (PSC), a patient's expectation and their satisfaction of treatment, physical examination, progression of osteoarthritis and the occurrence of adverse events.

**Cost-effectiveness and Budget Impact Analysis:** We will perform a cost-effectiveness and cost-utility analysis from societal perspective. For this we will measure productivity losses and the use of healthcare services. All relevant costs will be measured, valued and analyzed. Cost-effectiveness ratios and planes will be established using bootstrapping techniques (5000 replications).

A Budget Impact Analysis will be performed from societal, government and insurer perspective.

**Extent of burden:** In this multicenter randomized controlled trial, the current standard treatment, surgery, will be compared to conservative treatment, consisting of 16 sessions of structured physical therapy. Physical therapy is a safe treatment and is not known with any risks or complications. Since patients from the conservative group will be able to undergo delayed surgery when conservative treatment has failed, we are convinced this study is safe and without any additional risks.

### 3. INTRODUCTION AND RATIONALE

#### **Probleemstelling / Problem definition**

Meniscal surgery is the most performed orthopaedic surgical intervention with 30,000 procedures annually (1). In the U.S. there was a 49% increase in arthroscopic partial meniscectomies (APM) between 1996 en 2006 (2). Half of these were performed in patients over 45 years old. These numbers continue to rise since the proportion of population over 60 years will double from 11% to 22% between 2000 and 2050 (WHO). APM therefore contributes significantly to the costs of our health care system.

APM is the current treatment of choice for meniscal tears. When symptoms persist or in case of mechanical obstruction (locking and limited range of motion) APM has been proven to be an effective treatment to restore knee function (1;3). In older patients when mechanical obstruction is usually absent, it is unclear whether surgery is superior over conservative treatment to reduce symptoms.

Despite the wide use of APM for treatment of non-obstructive meniscal lesions, Randomized Controlled Trials (RCTs) on this subject are sparse. Howell (2009) (4) described in a Cochrane review that no conclusions could be drawn on a favorite role of surgery or conservative treatment due to a lack of RCTs. However, this review is out-of date and currently being updated by Mutsaerts et al. (5).

We have found only 4 RCTs (3;6-8) that compared surgery with conservative treatment in patients with meniscal tears. All these studies found no difference in outcome between groups. However, the power of these studies was too small to establish or rule out a true difference in effectiveness and the heterogeneity between the studies was too large to pool the data. It therefore remains unclear whether APM is more effective compared to conservative treatment on functional outcome.

Although arthroscopy for obstructive meniscal tears is widely accepted, non-obstructive complaints may not be triggered by meniscal tears, but by early onset osteoarthritis (OA) in older patients. This is strongly supported by a study of Englund (2008) (9) who identified meniscal tears on MRI in 61% of nearly 1000 asymptomatic volunteers over 50 years old. Treatment of non-obstructive meniscal tears focuses on reducing symptoms, while the meniscal tear itself might be asymptomatic and APM only reduces its function.

Furthermore, wide-spread utilization of arthroscopy in patients with knee OA came under scrutiny since two publications in the New England Journal of Medicine on arthroscopy for OA showed no benefit from arthroscopy over sham surgery (10;11).

Since quality of the menisci decreases with ageing and they become more vulnerable to damage and tears (12-14), both surgery and conservative treatment may not prevent the development of OA. However, APM in degenerative knees may accelerate this process more than a non-operative approach. This may therefore influence the number of knee arthroplasties subsequently needed. Faster progression to OA will lead to more patients on waiting lists for knee replacement and subsequently raise costs. In 2003, the National Hospital Discharge Survey in the U.S. described a total of 402,100 knee arthroplasties in 2003 and predicted this to grow with 673% to 3.48 million by 2030 (15), indicating its relevance. Preventing the acceleration of OA may result in stagnation of these numbers. A substantial reduction of costs of healthcare utilization could be accomplished.

Lastly, reducing the number of surgeries may result in less iatrogenic damage to cartilage in the knee and less adverse events related to surgery, which also leads to an improvement of patient outcomes and a reduction of costs.

A meniscal tear could thus lead to knee OA, but knee OA could also lead to a spontaneous meniscal tear (16).

We therefore hypothesize meniscal tears not as predominant factor causing knee symptoms in patients over 45 years and see an opportunity for conservative treatment.

#### **HEALTH CARE EFFICIENCY PROBLEM:**

There is thus a large health care efficiency problem as in older patients with non-obstructive symptomatic meniscal tears, expensive surgery is widely applied though there is no evidence that this approach is more effective compared with less costly conservative treatment.

**RELEVANCE FOR PRACTICE:**

The present study proposal is relevant for several reasons.

1. Meniscal surgery is the most performed orthopaedic intervention.  
Each year approximately 30.000 meniscal surgeries are performed in the Netherlands and half of these are performed in patients over 45 years old. Surgery is the current standard therapy for this patient group. With ageing of the population and the recent changes of reimbursement of physical therapy, it is expected that the number of meniscal surgeries will only increase further.
2. The standard therapy is performed despite a lack of evidence in times of evidence-based medicine.
3. Potential cost savings with the rising costs of health care system.  
As mentioned above, 15,000 meniscal surgeries are performed annually in the Netherlands in patients over 45 years. We estimate that 2/3 of surgeries can be prevented, which besides an estimated cost reduction of €12 million each year leads to less iatrogenic damage and fewer adverse events.
4. Investigator initiated research.  
Lexchin et al. (2003) (17) showed that pharmacy involvement in or sponsoring of clinical trials clearly influences research outcome, indicating there is a strong need for independent investigator initiated studies. This investigator initiated trial has, despite of possible negative consequences for surgeons in terms of fewer surgical procedures, only one aim in optimizing a patient's quality of life.
5. Progression of osteoarthritis.  
We are uninformed about the progression of OA after meniscal surgery. A reduction of surgery for meniscal tears in patients with OA might reduce the progression of OA, which could lead to a stagnation of patients on waiting lists for total knee replacement.

#### **4. OBJECTIVES**

The objective of this study is to evaluate the effectiveness and cost-effectiveness of surgical and conservative treatment of non-obstructive meniscal injuries in older patients

Hypothesis:

We assume equal improvement of physical function in both groups and reduced costs with conservative treatment.

## 5. STUDY DESIGN

We plan a non-inferiority multicenter RCT with an economic evaluation alongside. The study conducted by the Orthopaedic Research Consortium Mid-West Netherlands. Patients will be randomized into 2 equal groups of 160 patients and will receive either APM or PT.

### PRIMARY OUTCOME:

Primary outcome will be change in physical function from baseline to 2 years measured by the International Knee Documentation Committee (IKDC) 'Subjective Knee Form', which has been validated for meniscal injuries (18).

In addition, we will perform an economic analysis alongside the RCT from a societal perspective and a budget impact analysis from societal, government and insurer perspective.

### SECONDARY OUTCOMES:

#### 1) Change in:

- General health, measured by RAND-36;
- Quality of life, measured by EQ-5D5L;
- Pain, measured with the VAS both in rest and weight bearing;
- Level of activity, measured by Tegner Activity Scale (TAS);
- Patient specific complaints measured by the PSC (patient specific complaints) Questionnaire;
- Treatment group; number of patients initially treated conservatively, treated secondarily by APM.

We will use the EQ-5D5L to measure Quality Adjusted Life Years (QALY).

2) Productivity losses and the use of healthcare services, measured by a modified version of the Trimbos/iMTA questionnaire for Costs associated with Psychiatric Illness (TiC-P).

3) Relation between a participants expectation of treatment and their satisfaction.

4) Physical Examination (PE), consisting of performance on physical tests (squatting with duckwalk, Thessaly test, McMurray), the range of motion, joint line tenderness and the existence of joint effusion in the knee.

#### 5) Adverse events including:

- Minor: prolonged synovial fluid leakage from arthroscopy portals and bleeding
- Moderate: surgical site infection, vascular and neurological damage
- Severe: septic arthritis, cardiac events, pulmonary embolism and death

Surgical instrument malfunction will be recorded, as well as reoperations including knee arthroplasties and re-hospitalization.

6) We plan a follow up moment at 60 months to see the progression of osteoarthritis, measured with the Kellgren Lawrence Grading Scale for Osteoarthritis (appendix C).

X-ray and MRI will both be made at baseline, X-ray will be repeated after 2 and 5 years of follow up. All MRI's will be evaluated by describing the quality of the meniscus based upon signal intensity and the type of tear; longitudinal, horizontal or radial. All other structures, especially the other ligaments in the knee, will be judged as well. This will be done experienced radiologist, specialized into musculoskeletal radiology.

In order to get compatible results, randomization will be stratified for age. The activity level will also be assessed at baseline. This will be done by the Tegner scale and Activity Rating Scale (ARS).

### FOLLOW-UP:

Patients will visit the outpatient department for physical examination (3 months) and X-rays (24 months). All measurement outcomes will be obtained at baseline, 3, 6, 9, 12, 18 and 24 months, online or by hardcopy if preferable. Patients will be examined by a well experienced clinician at each site. The anticipated enrolment period will be approximately one year with follow up.

We also plan to perform another long-term outcome measurement after 5 years.

Endpoint: the first results of the study will be evaluated after 1 year of follow up. The endpoint for the primary outcome of the study will be after 2 years of follow up. However, we plan a follow up moment at 60 months to see the progression of osteoarthritis, measured with the Kellgren Lawrence Grading Scale for Osteoarthritis.

Sample size calculation:

Sample size is based on a power of 90%, an alpha of 0.05, a standard deviation of 18 points and a non-inferiority threshold of 8 points on the IKDC 'Subjective Knee Form'.

We calculated that with 10% loss to follow-up after 24 months and 25% delayed APM in PT group, 160 patients are needed per group in this equivalence type RCT. This means a total of 320 patients will be included. Sample size is calculated for the intention-to-treat analysis.

Assigning patients to treatment groups:

After signing and dating the informed consent form, patients will be randomized. This will be done in a web-based system, using the ALEA software, stratified for each site and for 2 age subgroups:

Subgroup 1: 45-57 years of age

Subgroup 2: 58-70 years of age

Patients who are excluded from the study will get treatment at the discretion of the surgeon. Patients who prefer not to participate will be asked for their reasons. These reasons will be recorded.

Data Management:

Database management will be done using a web-based system.

Safety: the occurrence of adverse events and subsequent knee surgeries will be queried and recorded at follow-up visits.

[figure not shown]**Figure 1: Study Flowchart**

\* Total follow up time for primary outcome in delayed APM group remains 24 months

CRF s\* = surgery / CRF c\*=conservative, CRF d\*=delayed

## 6. STUDY POPULATION

### 6.1 Population (base)

#### STUDY POPULATION:

We will include 320 patients between 45 and 70 years with symptomatic, non-obstructive MRI confirmed meniscal tears. We will study female and male patients of different ethnic backgrounds. Block randomization and database management will be done using a web-based system.

### 6.2 Inclusion criteria

- 1) Patients between 45 and 70 years of age at presentation.
- 2) A meniscal tear visualized on MRI. The meniscal tear can either be isolated or combined with a partial asymptomatic Anterior Cruciate Ligament (ACL) injury or a asymptomatic degenerative ACL shown on MRI with no abnormal clinical findings (a negative Lachman test and Pivot Shift).
- 3) Mental Competence.
- 4) Willingness to comply with follow-up schedule.
- 5) Written informed consent.

### 6.3 Exclusion criteria

- 6) Knee locking or trauma leading to acute surgery.
- 7) One of the following associated injuries on the index knee:
  - a. A symptomatic partial ACL rupture or any total ACL rupture determined by clinical examination (positive Lachman test and/or positive Pivot Shift) and shown on MRI;
  - b. A complete PCL injury;
  - c. Cartilage change down to bone; grade 4 of the Kellgren Lawrence Grading Scale for Osteoarthritis visualized on X-ray;
  - d. An injury to the lateral/posterolateral ligament complex with significantly increased laxity.
- 8) A history of knee surgery other than diagnostic arthroscopy on the index knee.
- 9) Tumors on MRI suspected for a malignancy.
- 10) Obese patients with BMI > 35.
- 11) ASA 4-5 (appendix D) patients which can interfere with revalidation.
- 12) General disease that effects physical function or systemic medication/abuse of steroids (e.g., rheumatoid arthritis, psoriatic arthritis, systemic lupus erythematosus, gout, pseudogout)
- 13) Any other medical condition or treatment interfering with the completion or assessment of the trial, e.g. contraindications to MRI or surgery.
- 14) Drugs or alcohol abuse.
- 15) Patients unable to speak or read Dutch.

#### **Nature and extent of the burden and risks associated with participation, benefit and group relatedness:**

At baseline, when a meniscal tear is suspected at presentation, an MRI-scan will be obtained. This is not seen as an extra burden for participants, since an MRI which has a high sensitivity and specificity normally is usually made to avoid unnecessary diagnostic arthroscopies as stated in the guideline for arthroscopy of the knee, 2010 (NOV) (1).

All patients approached and willing to participate in the trial will be randomized when all inclusion criteria are met when they return to the outpatient department for the results of the MRI.

Participants will be randomized into the surgical group or the conservative group and are followed at 3, 6, 9, 12, 18 and 24 months.

The risks associated with participation in the trial include the general risks for surgery, e.g. infection, bleeding, postoperative numbness, paralysis, pain, persistence of symptoms when randomized into the surgical group. In the conservative group, no specific risks are known to occur. Since surgery is current standard treatment, there are no additional risks for participation in this trial.

All patients will return to the outpatient department after 3 and 24 months. This will be for PE (3 months) and X-rays (24 months).

We plan a follow up moment at 60 months to see the progression of osteoarthritis, measured with the Kellgren Lawrence Grading Scale for Osteoarthritis.

The burden of the extra X-ray will be negligible, especially when focused on the potential outcome of the trial, which could lead to a significant reduction of unnecessary surgeries.

All questionnaires will be obtained digitally and can be completed at home. If preferred, a hardcopy can be sent to these participants.

Completion of the questionnaires will take approximately 30 minutes. The questionnaires at 9 and 18 months consist only of the EQ-5D-5L and TiC-P and will take only 5 minutes to complete.

#### 6.4 Sample size calculation

Sample size is based on a power of 90%, an alpha of 0.05, a standard deviation of 18 points and a non-inferiority threshold of 8 points on the IKDC (a minimal clinical important change in IKDC is 8.8) (18).

We calculated that with 10% loss to follow-up after 24 months and 25% delayed APM in the PT group, 160 patients are needed per group in this non-inferiority RCT.

This corresponds to a total of 320 patients will be included.

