7) We assume equal improvement of complaints in activities and movements found most important by patients (patient specific complaints).

8) We expect a greater reduction of joint line tenderness in the arthroscopic partial meniscectomy group shortly after therapy, compared to the physical therapy group, since part of the damaged meniscus is released. However, we expect no difference in joint line tenderness on the long term. We expect a faster reduction of joint effusion after treatment in the physical therapy group. However, we do not expect a difference between both groups after 24 months. We do not expect a significant improvement of ROM after treatment in both groups.

9) We estimate that 2/3 of surgeries can be prevented (as stated by Herrlin SV et al. (6), and therefore expect 1/3 of patients who will undergo delayed arthroscopic meniscectomy after completion of physical therapy. The possible cost reduction of this effect will be calculated in the economic analysis.

10) Patients in the physical therapy group will leave work for at least 16 sessions of 30 minutes each week, representing one working day, with the addition of travelling time. Patient in the surgery group are expected to be absent from work for one working day, the day of surgery. We therefore expect surgery to lead to more productivity losses.

11) We expect squatting to have the greatest predictive value of the different meniscal tests for detecting meniscal injuries.

12) We expect a faster development or progression of osteoarthritis after arthroscopic partial meniscectomy compared to physical therapy.

13) We expect adverse events to occur more frequently in the arthroscopic partial meniscectomy group. Patients who are subjected to delayed surgery after physical therapy has failed, remain in the physical therapy group. Therefore, we do expect adverse events to occur in the physical therapy group. Since the number in the arthroscopic partial meniscectomy group are to be expected to outnumber the number of patients with delayed surgery, we expect more adverse events in the arthroscopic partial meniscectomy group.

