## 10. STATISTICAL ANALYSIS

Data-analysis and presentation:

To investigate the effect of surgery, we will use generalized estimating equations (GEE) for longitudinal analysis in SPSS 18 on an intention-to-treat and per-protocol basis, as well as sub-group analysis of the cross-over patients. This method takes into account the dependency of observations within a patient, and the fact that not all patients may be assessed at each time point (missing data). In the primary GEE model, the outcome variable studied (e.g. physical function on the IKDC) will be analyzed as a dependent variable, using treatment allocation (1, intervention; 0, control) and time as a key independent variables. In the secondary GEE model, the outcome variables studied (e.g. general health on the RAND36, quality of life on the EQ5D-5L, level of activity on the TAS, knee pain on the question 10 of IKDC, the correlation between a patient's expectation and satisfaction, productivity losses on TiC-P, muscle strength, range of motion, squatting and adverse events) will be analyzed in a similar way. To evaluate whether the two groups differed in change over time the interaction term of group and time (group X time) will be assessed. Time will be included as a dummy variable (reference = baseline T0), and four interaction terms will be analyzed (T1Xgroup; T2x group; T3x group, T4x group). All models will be corrected for center of inclusion and age group. In additional analysis, we will investigate the possible confounding effect (defined as more than 10% change in the parameter estimate for groupXtime) of 5 variables (body mass index, gender, profession, ASA-classification, the affected meniscus, the type of tear and the stadium of OA according to the Kellgren Lawrence Grading Scale for Osteoarthritis).

At the following time points following the treatment (T2, T3, T5 and T7) we will describe the incidence of revisions (intervention group) or treatment failures (=delayed APM, control group) using descriptives. After two years (T7) we will compare the incidence of development or progression of OA between groups using a chi-squared test (or Fisher's Exact as appropriate). For all analysis, a two-tailed value of  $p < 0.05$  is considered to be significant.

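### The 160 per group is labelled an intention-to-treat size but is reached only by treating delayed-APM patients as lost data; 90% is not the ITT power (about 96.5%), and the 25% conflicts with 1/3 elsewhere

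*Protocol*

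**What the plan says.** Protocol Section 6.4 bases the size on "a power of 90%, an alpha of 0.05, a standard deviation of 18 points and a non-inferiority threshold of 8 points" on the IKDC, and concludes that "with 10% loss to follow-up after 24 months and 25% delayed APM in the PT group, 160 patients are needed per group". Section 5 repeats the calculation, calls the design an equivalence trial where Section 6.4 says non-inferiority, and adds: "Sample size is calculated for the intention-to-treat analysis".

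On delayed APM the protocol says the following:

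- Section 7 (Delayed surgery group) analyses these patients in the PT group under ITT.
- The footnote to Figure 1 in Section 5 keeps their follow-up for the primary outcome at 24 months.
- Section 10 nevertheless expects, within the ITT analysis, a non-ignorable, intervention-related dropout of 25%, to be handled by weighted GEE.
- Section 8.1.2, hypothesis 9: the authors "therefore expect 1/3 of patients who will undergo delayed arthroscopic meniscectomy after completion of physical therapy".
- Section 3 (Relevance for practice): "We estimate that 2/3 of surgeries can be prevented".

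Section 6.4 does not say whether alpha is one- or two-sided. Section 10 does: "For all analysis, a two-tailed value of" p below 0.05 is the criterion, which for a non-inferiority comparison means 0.025 on the relevant side.

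**The concern.** Under ITT, a PT patient who later has APM still contributes a 24-month outcome in the PT arm. Such a patient is not lost, so dividing the sample size by 0.75 has no place in an ITT calculation. Delayed APM also arises only in the PT group, so there is no reason to inflate the APM arm for it.

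Two things are at stake. First, the stated 90% should be the power of the analysis it is attached to, and the crossover rate behind it should agree with the rest of the protocol. Second, a reader of Section 6.4 may believe that crossover has been dealt with. What crossover to the comparator does in an ITT non-inferiority analysis is pull the observed difference towards zero, and a larger n does not correct that.

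**Working it through.** **Inputs.** SD 18, margin 8, power 90%, 10% loss and 25% delayed APM (Sections 5 and 6.4); true difference 0 (equal improvement assumed, Section 8.1.2); 1:1 allocation (Section 8.2); two-tailed 0.05, taken as one-sided 0.025 (Section 10). The calculation is a simple comparison of two means; gains from repeated measures or covariates are ignored.

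**Reproducing the plan's figure.**

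n per arm = 2 x (1.96 + 1.2816)^2 x 18^2 / 8^2 = 106.4, so 107 (108 with the t distribution).

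| Adjustment | n per arm |
|---|---|
| 10% loss only: 107 / 0.9 | 119 |
| 10% loss, then 25% removed: 107 / (0.9 x 0.75) | 159 |
| Same, starting from 108 | 160 |
| Additive 35% removed: 106.4 / 0.65 | 164 |
| Equivalence (two one-sided tests at 0.05), 110 / (0.9 x 0.75) | 163 |
| One-sided 0.05, 86.7 / (0.9 x 0.75) | 129 |
| 10% loss with dilution factor: 106.4 / (0.9 x 0.75^2) | 211 |

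At margin 8, every variant that lands near 160 removes the 25% as if the data were lost, and does so in both arms. Adjusting for loss alone, or for dilution, does not give 160.

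**Power at 160 per arm.** Power = Phi(8/SE - 1.96), with SE = 18 x sqrt(1/n1 + 1/n2). Here 160 x 0.9 = 144; 144 x 0.75 = 108; 144 x 2/3 = 96.

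| Analysis | APM / PT | SE | Power |
|---|---|---|---|
| ITT, 10% loss, crossovers kept | 144 / 144 | 2.121 | 96.5% |
| 25% excluded from PT only | 144 / 108 | 2.291 | 93.7% |
| 1/3 excluded from PT only | 144 / 96 | 2.372 | 92.1% |
| 25% removed from both arms (apparent basis of the plan) | 108 / 108 | 2.449 | 90.4% |

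The stated 90% matches only the last row. With no true difference, ITT power is the same whether the crossover rate is 25% or 1/3, because no one is removed.

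**Crossover and the ITT difference (illustration only).** Assume that PT alone is truly 8 points worse and that every crossover fully regains the surgical result. The ITT difference is then 8 x (1 - c):

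- c = 25%: 8 x 0.75 = 6.0 points
- c = 1/3: 8 x 2/3 = 5.3 points

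Both lie inside the 8-point margin. Here, unlike in the ITT power at zero difference, the choice between 25% and 1/3 changes the answer.

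**The case against.** **The trial is not underpowered.** A reader might infer that the 90% is not achieved. The documents do not support that. ITT power is 96.5%, and excluding crossovers from the PT arm leaves more than 90% at either rate. A figure below 90% (about 87%, 96 per arm) appears only if 1/3 is deleted from both arms, and no planned analysis does this because delayed APM occurs only in the PT group. This objection stands in full.

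**The formula is not printed.** This is also true; the removal of crossovers is inferred. The inference is strong because 108 / 0.675 is exactly 160, the nearby variants share the same step, and Section 10 puts a dropout of the same 25% into the ITT analysis. It could be said that Section 6.4 is therefore consistent with Section 10. That only moves the conflict: Section 10 then disagrees with Section 7 and the Figure 1 footnote.

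**Alpha is not open.** One might read the bare 0.05 as one-sided. Section 10 settles it as two-tailed, and 160 reproduces at one-sided 0.025. A cross-reference is enough.

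**Dilution is not an error for the ITT question.** One might infer an inflated false-positive rate from the 6.0 and 5.3 points. That needs a true 8-point deficit and full catch-up by every crossover, neither of which the documents supply. For the strategy of starting with PT, a 6.0 or 5.3 point difference really is within the margin. The protocol also plans per-protocol and crossover subgroup analyses. What remains is that the conclusion should be worded for that strategy.

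**The 2/3 in Section 3 is a national savings estimate**, so it is weak evidence of a trial crossover rate. Hypothesis 9 is what turns it into an expected 1/3 in the trial's own PT group, and that does conflict with 25%.

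**Conclusion.** The concern holds as an error in the stated basis of the sample size, not as a shortfall. The 160 per group is attached to an ITT analysis but is reached only by treating delayed-APM patients as lost from both arms, contrary to Section 7 and the follow-up note in Section 5. The 90% is therefore not the ITT power, which is about 96.5% at 144 evaluable per arm; 119 randomised per arm would have given 90%. With crossovers excluded from the PT arm only, power is 93.7% (25%) or 92.1% (1/3). The planning rate is 25% in Sections 5 and 6.4 and 1/3 in hypothesis 9, with no explanation.

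These figures rest on SD 18, margin 8, no true difference, one-sided 0.025, 10% loss in each arm and an inferred inflation formula. The crossover-excluded figures also assume that the per-protocol set drops only PT patients who had delayed APM. The direction is over-powering for ITT, and the number of patients need not change.

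**What to change.** Keep 320 patients and correct the text:

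1. Sections 5 and 6.4: state one-sided 0.025 (in line with Section 10). Give ITT power of about 96% at 144 per arm and, separately, power with crossovers excluded from the PT arm (93.7% at 25%, 92.1% at 1/3). Say which analysis any allowance for delayed APM serves.
2. Sections 5, 6.4 and hypothesis 9: reconcile 25% with 1/3, or explain why they differ.
3. Section 10: correct the wording so that delayed-APM patients are not counted as a 25% dropout in the ITT analysis, and limit the weighted GEE to outcomes that are actually missing.
4. Section 5: replace the equivalence label with non-inferiority.
5. Section 10: state that the ITT result concerns PT with optional delayed APM, and that the per-protocol analysis addresses PT alone, with the caveat that it removes treatment failures from one arm.

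The cost is an amendment to the wording. No patients, visits or measurements are added.
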